### Exclusion criteria

The exclusion criteria are: planned or current pregnancy in the next two years; previous or planned bariatric surgery; currently following a weight-loss programme (defined as a structured, prescribed and monitored programme and not a self-regulated diet); non-English Speaking or with Special Communication needs that would preclude them from understanding the study materials and interventions. GP’s will exclude patients who are inappropriate to invite into the study, for example patients who are violent/terminally ill/have a history of an eating disorder. GPs will also be allowed to define any additional inclusion/exclusion criteria to meet local practice and will be asked to provide details on these for the reporting of the study. No further criteria will be imposed, thus capturing the population that would typically be referred to these treatments. Participants receiving other weight loss treatments, e.g. Orlistat, will not be excluded as such participants would still be eligible for commercial referrals in standard practice, but this will be adjusted for in the analyses. Participants will be randomised to intervention arms, and thus those receiving additional treatment should be evenly spread across the interventions and these treatments will be accounted for in the cost-effectiveness analyses.

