### Randomisation

At the first assessment, a member of the research team trained in taking informed consent will ensure that the participant understands the trial and has read the participant information sheet. They will confirm their eligibility for the study and obtain written consent for their participation in the trial. Participant details, including baseline weight, will be entered into an online database by a member of the research team.

The database will automatically assign participants with a valid recorded baseline weight to one of three interventions (BI, CP12, CP52). The randomisation sequence was generated by the trial statistician and allocates participants in a 2:5:5 allocation stratified by centre and gender, with a block size of 12. The sequence is unknown to research staff and participants.

Due to the nature of the intervention and the trial design, neither participants nor research staff will be blinded to the intervention allocation.

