### Statistical analysis

#### Analysis design

There is already good evidence to suggest that CP produces significantly greater weight loss than BI and in the event that CP is not better than BI then the comparison of the CP arms would not be of interest. Accordingly we will conduct a sequential analysis, which will preserve the Type 1 error of 5% without the need for a multiplicity correction such as Bonferroni. The sequential analysis will consist of the following 2 stages:

i) Test the one-sided hypothesis that weight loss in the CP groups combined is greater than the weight loss in the BI arm.

ii) If the first test is significant at the 5% significance level, then test the two-sided hypothesis that there is a difference between CP52 and CP12 weight loss at the 5% significance level.

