### Clinical effectiveness

The primary analyses will assess differences in mean weight change from baseline to 12 months between the intervention groups. In order to investigate the impact of missing data, four analysis approaches will be taken: completers only, baseline observation carried forward (BOCF), last observation carried forward (LOCF) and a missing at random (MAR) analysis using a variance components model. For the LOCF, BOCF and completers analyses, fixed effect models for continuous normal data will be fitted to the 12 month weight data. The fixed effects will be intervention group, centre and baseline weight. For the MAR analysis, a model for multivariate normal data with the same fixed effects will be fitted using measured weights at each time point using generalised least squares. Coefficient estimates and their 95% confidence intervals will be calculated for each fixed effect.

All assumptions of the models will be checked using appropriate graphs (eq a Q-Q plot of residuals to check normality, residuals versus predicted values to check homogeneity of residual variance.) If the residuals are not normally distributed then the dependent variable may be transformed to normality, if there is no such transformation then non-parametric methods will be considered.

Secondary analyses will include analyses of weight change at 3 and 24 months; changes in blood pressure, waist circumference and fat mass at 3, 12 and 24 months; changes in biochemical measures at 12 months. These will be analysed using the same regression based models. Numbers of participants in each group achieving ≥5% and ≥10% weight loss at 12 and 24 months will also be explored.

Summary tables will be produced to look at the demographic distribution of the sample (age, sex, initial weight, BMI); attendance rates; time course of attendance; website usage.

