### Cost effectiveness

#### Within-trial cost-effectiveness

The incremental cost-effectiveness ratio of the intervention is the main outcome of the economic evaluation and will be expressed as incremental costs per incremental change in weight/BMI for the within-trial evaluation. Cost items to be included will be the cost of the intervention (i.e. cost to NHS of referral packages and infrastructure related to the operation of the referral scheme), primary, secondary, and tertiary health care use associated with weight-related disease (especially diabetes, coronary heart disease, colon cancer, and musculo-skeletal disorders). At baseline, participants will complete a health care usage questionnaire covering health service attendances and any weight loss treatment for the previous 3 months. This questionnaire will be completed again at 3, 12 and 24 months. Analysis of uncertainty will be conducted with a non- parametric bootstrap of the sampled data to generate a cost-effectiveness acceptability curve showing the probability that the intervention is cost-effective at various willingness-to-pay thresholds per unit of outcome. The within-trial cost-effectiveness analysis will be conducted jointly with the outcome analysis in year 3 of the study. The data will also be incorporated into the economic model.

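### Gender is a stratification factor but is missing from every listed model, so standard errors will be slightly too large; the promised adjustment for other weight-loss treatment is assigned to no analysis

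*Protocol article*

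**What the plan says.** Under Randomisation, the article says that the sequence "allocates participants in a 2:5:5 allocation stratified by centre and gender, with a block size of 12".

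Under Statistical analysis, Clinical effectiveness, the terms for the completers, BOCF and LOCF models are given as a definite list: "The fixed effects will be intervention group, centre and baseline weight". For the missing-at-random analysis, "a model for multivariate normal data with the same fixed effects will be fitted". The secondary continuous outcomes are to use the same regression models. In that section sex appears only in the summary tables, as part of the "demographic distribution of the sample (age, sex, initial weight, BMI" and so on.

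Under Exclusion criteria, participants on other weight-loss treatments such as Orlistat are kept in the trial, "but this will be adjusted for in the analyses". The same paragraph adds that "these treatments will be accounted for in the cost-effectiveness analyses". Within-trial cost-effectiveness describes a baseline questionnaire "covering health service attendances and any weight loss treatment for the previous 3 months", repeated at 3, 12 and 24 months.

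**The concern.** When randomisation is stratified on a factor that predicts the outcome, the arms are balanced on it and the treatment contrast varies less from trial to trial. A model that omits the factor leaves its variance in the residual and reports a standard error larger than the real sampling variation. Intervals are then too wide, and the test rejects less often than its nominal level under the null. Here one stratification factor is in the model and the other is not, with no reason given.

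The second strand is a promise without a home: an adjustment is announced in the eligibility section, and no model in the analysis section contains it. Since weight-loss treatment is recorded both before and after randomisation, it is worth stating which record is meant.

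**Working it through.** **Inputs from the article** (Sample size calculation, Analysis design): 200 BI, 500 CP12, 500 CP52; SD 6 kg; differences of 2.3 kg (BI against combined CP, one-sided 5%) and 1.3 kg (CP12 against CP52, two-sided 5%).

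**The article's own power, reproduced by normal approximation**
- Test 1: SE = 6 × √(1/200 + 1/1000) = 0.4648; 2.3/0.4648 = 4.949; Φ(4.949 − 1.645) = 99.95%, as stated.
- Test 2: SE = 6 × √(2/500) = 0.3795; 1.3/0.3795 = 3.426; Φ(3.426 − 1.960) = 92.87%, as stated.
- Product: 92.82%, as stated.

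**Assumption.** The article gives neither a gender effect nor a gender mix. Let r² be the share of residual variance that gender explains after the listed terms, holding the total residual SD at 6 kg. I take r² = 2% and 5%. For scale, with a proportion q of men and a gender difference of g kg, r² = q(1 − q)g²/36. With 30% men, 2 kg gives 2.3% and 3 kg gives 5.3%.

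**Formulas for CP52 against CP12, with gender balanced by the stratification**
- The true sampling error of the contrast is SE × √(1 − r²), whether or not gender is in the model.
- With gender omitted, the model still reports SE, which is too large by a factor 1/√(1 − r²).
- Type I error, omitted: 2 × [1 − Φ(1.960/√(1 − r²))].
- Power, omitted: Φ((3.426 − 1.960)/√(1 − r²)).
- Power, included: Φ(3.426/√(1 − r²) − 1.960).

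| | r² = 2% | r² = 5% |
|---|---|---|
| √(1 − r²) | 0.9899 | 0.9747 |
| Interval too wide by | 1.0% | 2.6% |
| Type I error, gender omitted | 2[1 − Φ(1.980)] = 4.8% | 2[1 − Φ(2.011)] = 4.4% |
| Power, gender omitted | Φ(1.481) = 93.1% | Φ(1.504) = 93.4% |
| Power, gender included | Φ(1.501) = 93.3% | Φ(1.555) = 94.0% |
| Gain in power | about 0.3 points | about 0.6 points |

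The power with gender omitted must not be taken as 92.9%. That is its value at r² = 0; once gender matters, stratification has already reduced the true sampling error. Test 1 power stays above 99.9% throughout.

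**Simulation check.** There were 3000 runs per scenario, with three centres by gender, blocks of 12, 2:5:5 allocation and a residual SD of 6 kg within gender. Omitting gender gave no bias (mean error within about 0.01 kg). At an assumed gender effect of 4 kg, which is larger than the cases in the table, the mean reported SE was 0.396 without gender and 0.380 with it, and type I error was 4.3% against 4.8%. At 2 kg the power difference was 0.1 points.

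**Other weight-loss treatment.** No arithmetic is possible, because neither its prevalence nor its effect is given. Side by side, Exclusion criteria announces an adjustment, while Clinical effectiveness lists terms that do not include it and extends that list to the other models. The economic promise in Exclusion criteria is a separate sentence, so it does not discharge the first. Attendance data are placed in sensitivity analyses (Adherence), as are self-measured weights (Withdrawal); this adjustment is placed nowhere.

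**The case against.** The strongest reply is that nothing here threatens the trial's conclusions. That stands. The estimate is unbiased, the error is on the conservative side, the 5% limit in Analysis design is respected, and baseline weight is already in the model. A reader might infer that omitting gender throws away the balance gained by stratifying, or that the error rate is out of control. Neither follows. The arms remain balanced and the estimate keeps that precision; only the reported standard error fails to show it.

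On the second strand, the reply is that Exclusion criteria speaks of analyses in general, not of the primary model, so a secondary or sensitivity analysis could satisfy it. That also stands, and a claim that two sections contradict each other on the content of the primary model would go too far. A reader might also infer that treatment started after randomisation will be used as a covariate and will bias the comparison. The article does not propose this. The sentence concerns people already receiving such treatment at entry, and the later questionnaires are described for health-care use and costs.

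A further reply is that an unseen analysis plan may settle both matters. It may, but the article does not leave the covariates open. It fixes a list, and that list departs from its own stratification.

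**Conclusion.** The point holds as a small, conservative inefficiency plus a wording gap. Gender is used to stratify and then left out of all four primary approaches and the secondary models. On the assumed r² of 2% to 5%, the cost is intervals 1.0% to 2.6% too wide, a true type I error of 4.8% to 4.4%, and about 0.3 to 0.6 points of power in the CP52 versus CP12 test. If gender adds nothing beyond baseline weight, the cost is nil. The figures also assume complete 12-month weights in both CP arms and near-exact balance within strata. The article's stated power is correct and is not affected.

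The adjustment for other weight-loss treatment needs reconciling between two sections. No bias from it is shown.

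**What to change.** In Clinical effectiveness, insert gender in the list of fixed effects, so that it reads: intervention group, centre, gender and baseline weight. State that this applies to the completers, BOCF, LOCF and missing-at-random analyses and to the secondary models. The cost is one word; gender is already recorded for randomisation.

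For other weight-loss treatment, either name the analysis that fulfils the statement in Exclusion criteria and say that only use recorded at baseline enters as a covariate, or delete the clause. The baseline questionnaire already collects the item, so either choice is a change of wording only.

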### Biochemical measurements

Biochemical measurements are optional for participants and taken under separate consent. Blood samples will be taken by fully trained research staff in line with standardised operating procedures. For assessment appointments where blood will be taken (0 and 12 months), participants will be asked to attend in a fasted state (no food or drink for 12 hours prior to the appointment).

At baseline and 12 months, participants will provide a sample of whole blood for analysis of glucose, glycosylated haemoglobin (HbA1c) and lipid profile. At baseline, an additional sample of whole blood will be collected in an EDTA tube, frozen at −80 and stored for later extraction of DNA and outside the trial protocol.

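### For blood markers sampled only at 0 and 12 months, the four missing-data approaches reduce to two distinct analyses, and the MAR fit uses no interim information

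*Protocol article*

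**What the plan says.** Under Statistical analysis, Clinical effectiveness, the article explains the purpose of the approaches: "In order to investigate the impact of missing data, four analysis approaches will be taken". They are completers, BOCF, LOCF and MAR. The first three are fixed-effect models for 12-month weight with group, centre and baseline weight. For the fourth, "a model for multivariate normal data with the same fixed effects will be fitted using measured weights at each time point". Weight has visits at 0, 3, 12 and 24 months (Table 1).

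The same section then turns to secondary outcomes, including "changes in biochemical measures at 12 months. These will be analysed using the same regression based models".

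The Biochemical measurements section fixes the blood schedule: "For assessment appointments where blood will be taken (0 and 12 months), participants will be asked to attend in a fasted state". Table 1 and the outcome list agree with it. The section also states: "Biochemical measurements are optional for participants and taken under separate consent". The article gives no separate missing-data method for blood markers and names no auxiliary variable for the MAR model.

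**The concern.** LOCF and a repeated-measures MAR model differ from BOCF and completers only when something is observed between baseline and the endpoint, or after it. Weight has such visits and the blood markers have none. Methods built for a four-visit outcome are therefore passed to an outcome with one post-baseline value.

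Two things are at stake. First, a report with four analyses agreeing in pairs could be taken as robust when the agreement is forced. Second, the analysis labelled MAR would ignore weight at 3 and 12 months, which is scheduled for everyone who attends, including those who give no blood. Secondary hypothesis (iv) under Clinical effectiveness makes blood-marker superiority of CP over BI, and of CP52 over CP12, a formal question. The Discussion expects many participants to miss some measurements.

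**Working it through.** The article gives no figure for blood markers or for missing-data bias, so there is none to reproduce on this point. (Its power figures for weight do reproduce, at 0.99952, 0.92865 and product 0.92821, but have no bearing here.)

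**Step 1: LOCF against BOCF.** Let Y0 and Y12 be the marker at baseline and 12 months. If Y12 is missing, BOCF fills in Y0. LOCF fills in the latest earlier value, which can only be Y0. The filled datasets are the same, so the fits are the same. A participant with no baseline sample has nothing to carry forward under either rule.

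**Step 2: MAR against completers.** The model is Y12 = group + centre + baseline + error, with baseline as a fixed effect. A participant without Y12 supplies no response and adds nothing to the likelihood. With one response per person, generalised least squares is ordinary least squares on those with Y12, which is the completers ANCOVA.

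**Step 3: numerical check.** One simulated trial was used: 200/500/500 participants, three centres, missingness dependent on earlier values, 37% missing at 12 months. The rates, correlations and effects are assumptions. Entries are effects versus BI for CP12 / CP52, in SD units.

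| Approach | Visits 0/3/12/24 (as weight) | Visits 0/12 (as bloods) |
|---|---|---|
| Completers | -0.372 / -0.561 | -0.37202 / -0.56078 |
| MAR | -0.338 / -0.538 | -0.37202 / -0.56078 |
| BOCF | -0.245 / -0.408 | -0.24514 / -0.40843 |
| LOCF | -0.253 / -0.466 | -0.24514 / -0.40843 |

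Four answers become two. Standard errors also match within pairs (completers and MAR: 0.07691 / 0.07652). The identities in Steps 1 and 2 do not depend on the assumed rates. Modelling baseline as a response with a common mean gives the same group effects. Arm-specific baseline means give -0.380 / -0.597 on the change scale, but the article specifies baseline as a fixed effect.

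**Step 4: possible size of bias.** From the Sample size calculation section: losses of 1.05, 2.7 and 4.0 kg, SD 6 kg. Assumed: correlation of marker change with weight change 0.3; 3-month losses of 1, 3 and 3 kg; 3-to-12-month correlation 0.7; bloods missing more often with less 3-month loss (51% BI, 41% CP).

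- Expected CP-BI marker effect: 0.3 × 2.3/6 = 0.115 SD. Simulated full data: 0.116.
- Completers (= MAR): 0.101, and 1 - 0.101/0.116 = 13% too small.
- BOCF (= LOCF): 0.073, and 1 - 0.073/0.116 = 37% too small.
- Model adding 3-month weight: 0.118.
- At correlation 0.4, in the same order: 0.147, 0.124, 0.092 and 0.148.
- CP52-CP12 at correlation 0.3, varying the 3-month SD and the strength of dropout: 0.066-0.068 in full data and 0.065-0.067 in completers. Both CP arms have the same assumed 3-month loss, so selection cancels.
- BOCF for CP52-CP12: with 41% missing in both arms, about 1 - 0.41 = 0.59 of the contrast survives.

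Varying the assumed correlation and dropout model, with about 40-55% missing, completers is about 1-22% too small for CP-BI (0.001-0.034 SD). Many settings lie between 0 and 8%. BOCF/LOCF was 36-48% too small for CP-BI in the settings examined.

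**The case against.** The strongest reply is that the commitment is inferred. The four approaches are introduced for weight, and carrying values forward is a data rule, not a regression model. The secondary-outcome sentence does not name the missing-data set, and an analysis plan that is not shown may handle bloods differently. This stands in part. The carry-over is the natural reading but not an explicit one, so the point is conditional on it.

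A reader might infer that the missing-data checks fail altogether for bloods. The documents do not support that. Completers and baseline-carried-forward remain, they rest on different assumptions, and they differ clearly in the check. Completers ANCOVA is itself valid under MAR given group, centre and baseline.

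A reader might also attribute the 13% and 37% figures to the two-visit schedule. The 37% is ordinary BOCF shrinkage, which any schedule would show. The 13% depends on assumed dropout, since the article gives no missingness rate and no evidence that 3-month weight predicts missing bloods. It is also small beside sampling error. With 200 × 0.49 = 98 BI and 1000 × 0.59 = 590 CP participants observed, the standard error is √(1/98 + 1/590) = 0.109 SD. A bias of 0.116 - 0.101 = 0.015 SD is then 0.015/0.109 = 0.14 standard errors.

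**Conclusion.** The point holds in conditional form. If the weight approaches are applied to glucose, lipids and HbA1c, the four give two distinct results, whatever the dropout rate or effect size. Agreement within a pair carries no information, and the analysis labelled MAR uses no interim data. This rests on baseline entering as a covariate and on no auxiliary variables, both as the article is written.

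Any bias is a matter of assumption. With 40-55% of samples missing in relation to 3-month weight, completers understates CP versus BI by about 1-22%, with essentially no bias for CP52 versus CP12 when those arms lose similar weight by 3 months. BOCF/LOCF shrinks both contrasts by roughly 40%. The primary weight analysis and the sequential tests are unaffected. It is a cheap improvement worth making for secondary outcomes, not a threat to the trial's main conclusions.

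**What to change.** State which missing-data approaches apply to the blood markers. For these outcomes drop LOCF and the one-visit MAR fit, since each duplicates another analysis. Use multiple imputation, or a joint multivariate normal model, that includes arm, centre, the baseline marker and measured weight at 0, 3 and 12 months, among participants who consented to bloods. Keep completers, and BOCF if wanted, as sensitivity analyses.

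The weights are already scheduled, so no new data are needed. The cost is extra programming and an imputation model to specify in advance. The change addresses missing 12-month samples. It does not address self-selection into optional blood sampling, which should be acknowledged when the results are reported.

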### Sample size calculation

We based the power calculation on data from our previous trials [8,9] with an expected difference of 2.3 kg between BI and combined CP, 1.3 kg difference between CP12 and CP52 (for example, a weight loss of 1.05 kg in the BI arm, 2.7 kg in the CP12 arm and 4.0 kg in the CP52 arm), and an assumed standard deviation of 6 kg. The statistical testing will be performed sequentially firstly by comparing CP arms with BI and then only if significant to then test for a difference between CP12 and CP52. Power is optimised by allocating more participants to the CP arms where the smaller difference is expected. With a sample of 1200 participants allocated as 200 BI, 500 CP12 and 500 CP52, we will have 99.95% power for the first test, to detect a difference of 2.3 kg between BI and combined CP and 92.87% power to detect a difference of 1.3 kg between CP12 and CP52. The total power of the study will be 92.82%.

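### The secondary-outcome models name baseline weight as the only baseline covariate; naming each outcome's own baseline would be a minor, free gain in precision

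*Protocol article*

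**What the plan says.** All of this is in the Protocol article. Under Clinical effectiveness in the analysis section, the models for the primary outcome are specified first: "fixed effect models for continuous normal data will be fitted to the 12 month weight data". Their covariates follow: "The fixed effects will be intervention group, centre and baseline weight". The missing-at-random analysis repeats the set: "a model for multivariate normal data with the same fixed effects will be fitted using measured weights at each time point".

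The same section then lists the secondary outcomes, among them weight change at 3 and 24 months and "changes in blood pressure, waist circumference and fat mass at 3, 12 and 24 months; changes in biochemical measures at 12 months". For the whole list it adds: "These will be analysed using the same regression based models". It gives no separate covariate list for any secondary outcome.

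The baseline values are collected. Table 1 schedules fat mass, waist, blood pressure, glucose, lipids and HbA1c at the baseline visit, and Biochemical measurements confirms this for the optional blood samples: "At baseline and 12 months, participants will provide a sample of whole blood for analysis of glucose, glycosylated haemoglobin (HbA1c) and lipid profile". Under Randomisation, the sequence "allocates participants in a 2:5:5 allocation stratified by centre and gender, with a block size of 12", so balance on these markers is left to chance.

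**The concern.** In the weight model, baseline weight is the outcome's own baseline, and the model is an ordinary ANCOVA. Moved unchanged to HbA1c, LDL or blood pressure, the same covariate is no longer the outcome's baseline. The model becomes a change score adjusted for a different variable. Regression to the mean in the marker is then left in the residual, and part of any chance baseline difference enters the arm contrast.

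The wording also hides a choice. For weight, modelling change or modelling the 12-month value gives the same arm coefficient, because baseline weight is in the model. For a marker adjusted only for baseline weight, the two give different estimates and different standard errors. At stake are precision and an unambiguous specification for outcomes on which the Secondary objectives state directional hypotheses. Research staff are not blinded to allocation, so the choice is better fixed in advance.

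**Working it through.** **The plan's own figures.** The only power figures concern weight. The inputs, from Sample size calculation and Analysis design, are 200, 500 and 500 participants, SD 6 kg, differences of 2.3 and 1.3 kg, a one-sided 5% first test and a two-sided 5% second test.
- Test 1: SE = 6 × √(1/200 + 1/1000) = 0.465; 2.3/0.465 = 4.95; power = Φ(4.95 − 1.645) = 99.95%, as stated.
- Test 2: SE = 6 × √(2/500) = 0.379; 1.3/0.379 = 3.43; power = Φ(3.43 − 1.96) = 92.87%, as stated.
- Product: 92.82%, as stated.

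These figures reproduce, and the present point does not touch them.

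**Assumptions for the secondary outcomes.** The article gives no SD or correlation for any marker. Let ρ be the correlation of a marker's baseline with its follow-up value (equal variances, scaled to 1). Let r be the correlation of the marker's baseline with baseline weight, and rρ that of its follow-up value with baseline weight. I take ρ = 0.5 to 0.9, r = 0.1 to 0.3 for blood pressure and blood markers, and r = 0.7 to 0.85 for waist and fat mass.

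**Residual variances.**
- Own-baseline ANCOVA: 1 − ρ².
- Change adjusted for baseline weight: 2(1 − ρ) − r²(1 − ρ)².
- Ratio of the second to the first: [2 − r²(1 − ρ)]/(1 + ρ).

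Example: r = 0.1, ρ = 0.5 gives (2 − 0.005)/1.5 = 1.330, and √1.330 = 1.153, a standard error 15.3% larger.

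Excess in standard error over own-baseline ANCOVA, change as the response:

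| ρ | r = 0.1 | r = 0.3 | r = 0.7 | r = 0.85 |
|---|---|---|---|---|
| 0.5 | 15.3% | 14.2% | 8.2% | 4.5% |
| 0.6 | 11.7% | 10.8% | 6.2% | 3.4% |
| 0.7 | 8.4% | 7.7% | 4.4% | 2.4% |
| 0.9 | 2.6% | 2.4% | 1.3% | 0.7% |

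With r = 0 the ratio is 2/(1 + ρ). Own-baseline adjustment then cuts the standard error by 1 − √((1 + ρ)/2), which is 13%, 11% and 8% at ρ = 0.5, 0.6 and 0.7.

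**Chance imbalance.** With full data ("With a sample of 1200 participants allocated as 200 BI, 500 CP12 and 500 CP52"), a baseline difference has SE √(1/200 + 1/1000) = 0.077 SD for BI against the combined CP arms and √(2/500) = 0.063 SD for CP12 against CP52. A change-score contrast moves by −(1 − ρ) times the baseline difference, less any part explained by baseline weight. A one-SE imbalance in BI against CP therefore shifts the estimate by 0.077 × 0.5 = 0.039 SD at ρ = 0.5 and 0.077 × 0.3 = 0.023 SD at ρ = 0.7. Relative to the contrast's own standard error (ignoring baseline weight) this is √((1 − ρ)/2), or 0.50 and 0.39. Bloods are optional, so the imbalance SE would be larger for those markers; the article gives no uptake figure.

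**The case against.** The strongest objection is that the text never says the own baseline is left out. The sentence cannot be carried over word for word in any case, since the response must change from weight to the marker. Replacing the baseline covariate along with it is at least as natural, and then the loss is zero. The sentence also covers weight at 3 and 24 months, where baseline weight is the correct covariate. This stands, so the point is an ambiguity with an inefficient literal reading. Against it, the same section uses the word same for an identical covariate set in the missing-at-random model, though there too the outcome is weight.

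Second, covariates for each secondary outcome usually belong in a statistical analysis plan, which is not shown here. Mere silence would be no finding. But the article is not silent: it names a covariate and then extends the models to other outcomes.

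Third, a reader might infer larger harm than the article supports.
- **Bias.** Randomisation keeps the contrasts unbiased on average. The outcomes are changes, so the own baseline already enters by subtraction, and only about (1 − ρ) of an imbalance carries over, in the opposite direction.
- **Bigger precision losses.** If follow-up values were modelled with baseline weight alone, the variance ratio would be (1 − r²ρ²)/(1 − ρ²), for example (1 − 0.0049)/0.51 = 1.95 at r = 0.1, ρ = 0.7. The article lists these outcomes as changes, so this is not the model to charge it with.
- **Baseline weight as a poor proxy throughout.** This is doubtful for waist and fat mass, which can be expected to correlate closely with weight. Their loss is correspondingly small.

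**Conclusion.** The point holds as a minor, free improvement. Followed literally, the stated model adjusts the secondary outcomes for baseline weight and not for their own baseline. With change as the response, standard errors for blood pressure and blood markers are then about 8-15% larger than they need be at ρ = 0.5 to 0.7, falling to 2-3% at ρ = 0.9. For waist and fat mass the excess is about 2-8% at ρ = 0.5 to 0.7 and about 1% at 0.9. These sizes rest on assumed correlations, because the article supplies none. If own baseline was meant all along, the loss is nil and only the wording needs attention. Neither reading shows a biased analysis, and neither affects the primary outcome, the error control or the sample size.

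**What to change.** Under Clinical effectiveness, state that each continuous secondary outcome is analysed with arm, centre and the baseline value of that same outcome as fixed effects. Baseline weight may stay as an additional covariate. Once the own baseline is in the model, change and follow-up value give the same arm coefficient, so the question of which response is modelled also disappears.

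The cost is one sentence, best added before the secondary outcomes are analysed. The baseline measurements are already scheduled, so there is no burden on participants or sites. No one is lost from the analysis either, because a change score already requires the baseline value.
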